### Randomization and Blinding

After the baseline survey in October 2020, a total of 4 clusters each with 45 farmers were randomly assigned to one of the three arms, comprising 180 farmers per arm (Figure 1): (1) educational intervention, (2) educational intervention+RANAS-based SMS text messages, or (3) control group. One of the Swiss investigators who had no previous knowledge of the subcounties used Microsoft Excel (Microsoft Corp) random numbers to randomize the clusters to the arms. The allocation of the clusters was concealed from the participants. The participants were also blinded with regard to which arm other farmers had been assigned to. The investigators and facilitators knew which arm the farmers had been assigned to, and at the follow-up interviews, the research assistants could know which arm the farmers had been assigned to.

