### Sample Size Calculation

We estimated a sample size of 540 farmers that assumed a statistical power of 80% based on the estimated observed differences between the EISs of an average pesticide application between smallholder farmers who received training in pesticide handling and those who did not receive it in a recent survey in Uganda [23]. The trained group had a mean EIS of 0.47 (SD 0.10), and the untrained group had a mean EIS of 0.55 (SD 0.18). We assumed that the 2 planned intervention arms would show a similar effect distribution. Hence, we based our sample size calculation on the 2-sample means test assuming a cluster-randomized design, a total of 12 clusters equally distributed between the control and intervention groups, and an intraclass correlation coefficient of 0.4. The package *power two means* in the statistical software Stata (version 15; StataCorp) resulted in a cluster size of 40 farmers and a total of 480 farmers, which would reach a power of 80% at a significance level of 5%. To account for a possible dropout rate of 13% at follow-up based on a previous study in a similar setting [23], in each cluster, an additional 5 farmers were enrolled, hence constituting a total sample size of 540.

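### With the stated ICC of 0.4, 12 clusters of 40 farmers give about 31% power (about 23% for 4-versus-4 contrasts), not 80%, and no cluster size reaches 80%

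*Protocol article*

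**What the plan says.** The section Sample Size Calculation of the protocol article gives a complete set of inputs. The effect comes from an earlier Ugandan survey: mean EIS 0.47 (SD 0.10) in trained and 0.55 (SD 0.18) in untrained farmers. The method is a two-sample means test for a cluster-randomised design, with "a total of 12 clusters equally distributed between the control and intervention groups, and an intraclass correlation coefficient of 0.4". The Stata command is said to have "resulted in a cluster size of 40 farmers and a total of 480 farmers, which would reach a power of 80% at a significance level"; that level is 5%. Five farmers per cluster were then added for dropout, making 540.

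The section Randomization and Blinding describes a different split: "a total of 4 clusters each with 45 farmers were randomly assigned to one of the three arms". The section Statistical Analyses tests control against education and against education plus SMS, and compares the two intervention arms with each other in an additional model for PPE and glove use.

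**The concern.** An ICC of 0.4 is very large for clusters of 40. At that value nearly all the information lies in the number of clusters, and there are only 12. A result of 40 farmers per cluster with 80% power is therefore implausible on its face. The calculation also splits the clusters into two groups of 6, whereas the trial has three arms of 4.

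This is the article's only power statement, and the outcome results are still to be published. If the 80% stands, a null finding on EIS will be read as fair evidence against an effect of the planned size. Under the article's own assumptions the design would miss that effect in about 69% of trials with 6 versus 6 clusters, and in about 77% with 4 versus 4.

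**Working it through.** **Inputs** (Sample Size Calculation, unless noted)

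- Difference 0.55 − 0.47 = 0.08.
- Sum of variances 0.10² + 0.18² = 0.0424.
- Cluster size m = 40, ICC 0.4, 5% level. Sidedness is not stated; two-sided is assumed.
- 6 versus 6 clusters in the calculation; 4 per arm in the trial (Randomization and Blinding).

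**Attempt to reproduce the stated 80%**

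1. Without clustering, the number needed per group is (1.96 + 0.84)² × 0.0424 / 0.08² ≈ 52.
2. Design effect = 1 + (m − 1) × ICC = 1 + 39 × 0.4 = 16.6.
3. Effective size per group, 6 versus 6: 6 × 40 / 16.6 = 240 / 16.6 ≈ 14.5, against 52 needed.
4. SE = √(0.0424 × 16.6 / 240) = 0.0542, and 0.08 / 0.0542 = 1.48. Power = Φ(1.48 − 1.96) ≈ 31% (27% with a t reference on 10 df).

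The 80% is not reproduced.

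**Can a larger cluster size help?** As m grows, the effective size per group approaches 6 / 0.4 = 15. Power then tops out at about 32%. With these inputs no cluster size gives 80%, so 40 cannot be the solution. At m = 40 the number of clusters needed is 52 × 16.6 / 40 = 21.6, about 22 per group (23 with a t reference).

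**The split that was randomised.** For 4 versus 4, SE = √(0.0424 × 16.6 / 160) = 0.0663, the ratio is 1.21, and power is about 23% (17% with t on 6 df).

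| Contrast, ICC 0.4, m = 40 | Power (normal) | Power (t, clusters − 2 df) | Power with unlimited m (normal) |
|---|---|---|---|
| 6 v 6 | 31% | 27% | 32% |
| 8 v 4 (intervention arms pooled) | 25% | 21% | 26% |
| 4 v 4 | 23% | 17% | 23% |

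**Detectable difference at 80% power** (normal): 2.80 × 0.0542 = 0.152 for 6 versus 6 and 2.80 × 0.0663 = 0.186 for 4 versus 4. These are 1.9 and 2.3 times the planned 0.08.

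**Other readings of the inputs**

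- One-sided test: 43% (6 v 6), 33% (4 v 4).
- One-sided with SD 0.10 in both groups, the most favourable variant tried for 12 clusters: 69%, or 71% with unlimited m.
- 12 clusters per group instead of 12 in total: 55%.
- ICC misprinted for 0.04, 6 v 6: 96% at m = 40, and 13 per cluster would already give 80%. This does not lead to 40 either.
- ICC at which m = 40 gives 80% (normal): (240/52 − 1)/39 = 0.093 for 6 v 6; (160/52 − 1)/39 = 0.053 for 4 v 4.

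**The case against.** The arithmetic itself is not in dispute. The objections concern how far it reaches.

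- **EIS is a secondary outcome.** The coprimary outcomes are KAP scores and PPE use, and the article gives no effect size, SD or ICC for the power of either. This stands: the 31% and 23% apply to EIS and should not be carried over.
- **Baseline adjustment.** The abstract plans baseline measures as predictors, which could raise real power. No correlation is given, so the gain is unknown. If adjustment removed half the variance at both levels (an assumption for illustration), power would be 55% for 6 versus 6 and 40% for 4 versus 4. The printed calculation is a plain two-sample test, so adjustment cannot explain its 80%.
- **Degrees of freedom.** One model with all three arms leaves about 12 − 3 = 9 df, not 6. The 4-versus-4 power is then 19% instead of 17%. This is fair for the comparisons with control; 6 df is right for a model holding only the two intervention arms.
- **Pooling.** Statistical Analyses codes both intervention arms as 1, so a pooled 8-versus-4 contrast is a possible reading. It has 25% power.
- **A misreported ICC.** An ICC near 0.05 with 4 versus 4 clusters gives about 82% at m = 40 (normal), close to the published result. That may be what was run, but the article states neither that ICC nor that split, and a t reference on 6 df brings the figure down to about 67%.

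None of these restores 80% from the inputs as printed.

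**Conclusion.** The paragraph is wrong as written. Its inputs give about 31% power, at most about 32% at any cluster size, and about 23% for a 4-versus-4 contrast. These figures assume a two-sided 5% test, a normal approximation, no baseline adjustment, and the 0.08 difference in each contrast; the article gives no separate effect for education versus education plus SMS. With a t reference they fall to 27% and 17%.

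The conclusion is conditional on the stated ICC. The true ICC is unknown and may be well below 0.4, so the document alone cannot tell an underpowered design from a misprinted input. It does show that the stated inputs and the stated result cannot both be right, and that the calculation uses a cluster split the trial does not have.

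**What to change.** Rewrite the section Sample Size Calculation:

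1. State the ICC and the cluster split actually entered, and correct whichever was misprinted.
2. Redo the calculation for 4 versus 4 clusters with a t reference and the achieved cluster size of about 41 (494 farmers followed up / 12 clusters).
3. Replace the 80% with the resulting power or detectable difference, and say that it refers to EIS.
4. Estimate the ICC from the 539 baseline interviews and show the result over a range such as 0.02 to 0.4. At an ICC of 0.04, for example, 4 versus 4 clusters of 40 give 87% (normal), 78% (t, 9 df) or 73% (t, 6 df).
5. In the results papers, do not describe a null finding as adequately powered on the strength of the present paragraph; interpret it from the confidence interval.

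The cost is rewording and a few minutes of calculation. Follow-up ended in October 2021, so the change affects reporting and interpretation only. The stated power will probably become less favourable, and no new farmers are needed.

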### Description of the Interventions

#### Educational Intervention

The investigated educational intervention is an existing training curriculum (Multimedia Appendix 2) designed by the UNACOH to reduce pesticide exposure and associated human and environmental health effects in Uganda between 2010 and 2020 [28]. It includes 5 modules: introduction to synthetic pesticides, pesticides and human health, pesticides and the environment, pesticide application equipment, and IPM. The main objective of the intervention was to improve pesticide handling through enhancing the KAP of smallholder farmers. Furthermore, the intervention is hypothesized to reduce pesticide exposure and the negative associated health symptoms.

The intervention was developed under the Pesticide Use Health and Environment (PHE) project and implemented in 3 phases by the UNACOH in collaboration with Diálogos, a Danish NGO. The project’s interventions included 3 thematic areas: evidence gathering or documentation, training or knowledge dissemination, and policy influence or lobbying and advocacy. Among the several project trainees were smallholder farmers, agro-dealers, extension workers, village health personnel, and health workers on topics such as responsible pesticide handling; IPM; and acute pesticide poisoning diagnosis, management, and reporting.

The educational materials used by the PHE project in its first phase (2010-2013) were originally adapted from a sister project, *Proyecto De Desarrollo Comunitario*, implemented in Bolivia with support from the same partner, “Dialogos.” A series of 7 small booklets or modular training guides was developed and used to facilitate training in the first 2 phases (2010-2013 and 2013-2017), and at the start of the third phase (2017-2020), they were revised and merged into 1 training manual or curriculum in technical partnership with and with approval from the Agricultural Chemicals Control Board; Department of Crop Protection; and Ministry of Agriculture, Animal Industry, and Fisheries of Uganda. Copies of this 5-module manual, titled “Responsible pesticide use and handling: A guide for sustainable pest management,” were widely disseminated by the Ministry of Agriculture, Animal Industry, and Fisheries through its structures.

#### RANAS-Based Text Messages

##### Overview

In addition to being delivered the educational training manual, one arm received mobile phone SMS text message reminders. The SMS text message intervention was based on the RANAS approach, a systematic approach for behavior change (see Multimedia Appendix 3 for detailed wordings of the messages). The RANAS approach is an established tool that suggests different steps for designing and evaluating evidence- and theory-based behavior change interventions, most importantly by informing intervention development through a baseline assessment (see step 1). Figure 4 outlines the 5 steps suggested by the RANAS approach and how these steps were applied to design the SMS text messages in this study. All steps have been successfully executed (see the ticked boxes in Figure 4) except for the evaluation phase, which will be reported in forthcoming papers. Thus, we promoted farmers’ PPE use as one behavior to substantially reduce pesticide exposure [23].

**Figure 4 figure4:**
[figure not shown]
Development and evaluation guide for the SMS text messaging intervention based on the steps to systematic behavior change from the Risks, Attitudes, Norms, Abilities, and Self-regulation (RANAS) approach [25] for this study. BCT: behavior change technique; PPE: personal protective equipment.

##### Step 1 of RANAS-Based Intervention Development: Identifying Psychosocial Determinants of PPE Use at Baseline

The core concept of the RANAS approach is that behavior change is driven by various psychosocial determinants that need to be in favor of new behavior [26,29]. On the basis of a synthesis of behavior change theories (eg, the health belief model [30] and the theory of planned behavior [31]), the RANAS approach describes 17 psychosocial determinants that are of potential relevance to change behavior. These are grouped into 5 categories of determinants (risks, attitudes, norms, abilities, and self-regulation). Table 1 outlines sample items for all determinants proposed by the RANAS approach, which can help understand their definition.

Risks comprise health knowledge, perceived vulnerability (estimates regarding the personal likelihood of catching a disease related to pesticides), and severity (estimates regarding the seriousness of a pesticide-related disease and its consequences).Attitudes include feelings (emotions arising when thinking of or practicing PPE use or thinking about its consequences, eg, being proud of using PPE) as well as beliefs about cost benefits, such as monetary and nonmonetary (eg, farmers’ perception of the fit of PPE and expenditure of time related to PPE use) costs and benefits of a behavior. These beliefs may also include response efficacy, which is the belief of successfully averting threats by using PPE.Norms include perception of descriptive norm (others’ behavior, ie, observation and awareness of PPE use practiced by others) and injunctive norm (perception of to what extent PPE use is typically approved or disapproved of by significant others and institutional norms), as well as personal importance (farmers’ belief of what the farmer should [not] do).Abilities include how-to knowledge (knowledge of how to obtain access to PPE) and confidence (perceived ability to execute and continue PPE use and recover from setbacks of not using PPE).Self-regulation includes action planning (attempts to plan for PPE use, eg, when, where, and how to buy or wear PPE), action control (attempts to self-monitor PPE use and correcting it toward a behavioral goal), barrier planning (attempts to plan to overcome barriers that would impede PPE use), commitment (the obligation that a farmer feels), and effort to practice PPE use.

**Table 1 table1:** Baseline results to identify relevant psychosocial determinants of personal protective equipment (PPE) use based on the Risks, Attitudes, Norms, Abilities, and Self-regulation approach—(1) intention to buy PPE, (2) intention to use PPE, (3) amount of PPE items owned, and (4) frequency of PPE use.

Predictor	Sample item	Amount of PPE items owned, β (SE)	Frequency of PPE use, β (SE)	Intention to buy PPE, β (SE)	Intention to use PPE, β (SE)
Intercept	N/A^a^	.47 (0.09)^b^	.27 (.08)^b^	.06 (.11)^b^	.34 (.07)^b^
Intention to buy PPE	How strong is your intention to buy all the recommended PPE items for your personal use?	.05 (.04)	.04 (.03)	N/A	N/A
Intention to use PPE	How strong is your intention to always wear all the recommended PPE items when handling pesticides in the future?	–.01 (.05)	–.04 (.05)	—	—
Vulnerability	How likely do you think it is that you will experience acute symptoms from using pesticides if you do not wear all the recommended PPE items?	–.00 (.05)	.01 (.04)	.15 (.06)^c^	.01 (.04)
Severity	Imagine you are experiencing acute symptoms of pesticide use, how severe do you rate the consequences for your own health?	.02 (.05)	–.03 (.05)	–.17 (.07)^c^	–.06 (.05)
Response efficacy	To what extent do you think that wearing all the recommended PPE items when handling pesticides can protect you from getting sick?	–.04 (.05)	.01 (.04)	.11 (.06)	.20 (.04)^b^
Attitude: costs	How expensive do you consider it to buy all the recommended PPE items?	–.09 (.04)^c^	–.08 (.04)^c^	–.01 (.05)	.02 (.03)
Attitude: fitting clothes	How fitting is the recommended PPE for you (eg, size and cut)?	.05 (.04)	.03 (.04)	.04 (.05)	–.01 (.04)
Attitude: time consuming	How time consuming do you think it is to put on all the recommended PPE items when handling pesticides?	.02 (.03)	.01 (.03)	.12 (.04)^d^	–.00 (.03)
Feeling: uncomfortable	To what extent do you feel that it is uncomfortable to always wear all the recommended PPE items when handling pesticides? (recoded)	.04 (.03)	.04 (.03)	.06 (.04)	–.01 (.03)
Feeling: proud	How proud would you feel if you wore all the recommended PPE items when handling pesticides?	.03 (.05)	.04 (.04)	.17 (.06)^d^	–.01 (.04)
Feeling: weak	To what extent would others think you are weak when wearing all the recommended PPE items? (recoded)	–.04 (.02)	–.03 (.02)	–.02 (.03)	.02 (.02)
Overall rate of benefit	Now, considering the potential disadvantages of wearing all the recommended PPE items against its advantages, how advantageous do you evaluate the use of PPE as recommended?	–.03 (.06)	.04 (.06)	.00 (.08)	.08 (.05)
Descriptive norm (others’ behavior)	How many farmers in neighboring farms are using all the recommended PPE items when handling pesticides?	.40 (.06)^b^	.36 (.05)^b^	–0.12 (.07)	.04 (.05)
Injunctive norm (others’ approval)	To what extent do you think that your wife (or partner) wants you to wear all the recommended PPE items when handling pesticides?	–.01 (.04)	.00 (.04)	.13 (.05)^c^	.01 (.04)
Personal norm	How important is it for you to wear all the recommended PPE items when handling pesticides?	–.01 (.07)	.02 (.07)	.15 (.09)	.07 (.06)
Action knowledge	Where would you go to buy all this equipment?	.05 (.02)^d^	.04 (.02)^c^	.01 (.02)	–.00 (.02)
Confidence	How confident are you that you can remember to wear all the recommended PPE items when handling pesticides?	.00 (.04)	–.01 (.04)	.08 (.06)	.04 (.04)
Action plan to buy PPE	Do you have a plan for how to buy all the PPE items to cover all body parts?	.06 (.05)	.03 (.04)	.23 (.06)^b^	.01 (.04)
Action plan to wear PPE	Imagine you have all the PPE items, do you have a plan to make sure you always wear them?	.05 (.04)	.10 (.04)^c^	.09 (.05)	.04 (.04)
Barrier planning	Do you have a plan for how to overcome these difficulties (that hinder you from wearing PPE)?	–.31 (.06)^b^	–.28 (.05)^b^	–.06 (.07)	–.01 (.05)
Commitment	How strongly do you feel committed to wearing the PPE items you have when handling pesticides?	.02 (.05)	.08 (.04)	–.04 (.06)	.06 (.04)
Effort	To what extent do you make a conscious effort to always wear all the recommended PPE items?	–.00 (.03)	.01 (.03)	.09 (.04)^c^	.18 (.03)^b^

^a^N/A: not applicable.

^b^*P*<.001.

^c^*P*<.05.

^d^*P*<.01.

##### Step 2 of RANAS-Based Intervention Development: Identifying Behavioral Determinants of PPE-Related Intentions and Behaviors at Baseline

Different contexts, behaviors, and persons may presuppose the expression of different psychosocial behavioral determinants, which need to be identified in a baseline assessment (step 2). To identify the determinants that are relevant when promoting PPE use among Ugandan smallholder farmers, we assessed all psychosocial determinants described by the RANAS approach at baseline (see the Outcome Measures section; ie, psychosocial determinants related to pursuing PPE use and using PPE). Multiple regression analyses were then computed to identify which determinants were related to higher behavior and intention to pursue PPE use and use PPE. In total, 4 regression models were calculated using the following dependent variables: intention to buy PPE, intention to use PPE, number of PPE items owned, and frequency of PPE use.

The baseline analyses of all 3 study groups before the interventions revealed that farmers owned PPE to cover an average of 4 (out of 8; SD 1.6) body parts. The accumulated frequency of using PPE to cover all body parts was 4.1 (SD 2.8), with a possible range of 0 (never covering any body part) to 40 (always covering all body parts). This mean corresponds to 10% (SD 7%) of full body, consistent use (always covering all body parts with PPE=100%). The regression analyses (Table 1) indicated the following:

Farmers’ intention to buy PPE was higher when they considered themselves more vulnerable to health risks, perceived the health risks of pesticides to be less severe, perceived wearing PPE as more time consuming, felt proud of using PPE, perceived other people to approve of PPE use more, and had an action plan for where to buy PPE, as well as when they were more committed to using PPE.Farmers’ intention to buy PPE was higher when they perceived higher response efficacy and were more committed to using PPE.Farmers owned more PPE items when they perceived the costs to be lower, perceived other farmers to use PPE, had an action plan for where to buy PPE, and had a coping plan in the sense of overcoming arising barriers to using PEE and pursuing more PPE.Farmers used PPE more frequently when they perceived the costs to be lower, perceived other farmers to use PPE, had an action plan for where to buy PPE, and had a coping plan in the sense of overcoming arising barriers to using PPE pursued more PPE.

##### Step 3 of RANAS-Based Intervention Development: Selecting Behavior Change Techniques and Designing Behavior Change Strategies

After identifying relevant psychosocial determinants of the healthy behavior (in this case, PPE use) at baseline, the RANAS approach suggests selecting behavior change techniques to promote the identified psychosocial determinants. In this way, farmers who are not yet adopting the behavior may be enabled to do so. Behavior change techniques are components of an intervention designed to enable behavior change by targeting psychosocial determinants that facilitate behavior change [32,33]. The RANAS catalog proposes which behavior change techniques to select to target each RANAS-based psychosocial determinant. The behavior change techniques that were used, as well as detailed wording of the developed SMS text messages, can be found in Multimedia Appendix 3.

#### Procedures of Educational Intervention

A 2-day workshop was held in the DFAs’ training facilities and delivered the curriculum based on the 5 modules (see Multimedia Appendix 4 for a summary of activities per module as well as coded behavior change techniques). The training was facilitated by the study coordinator, the author of the educational curriculum, who has >10 years of field experience facilitating similar trainings under the PHE project. In total, 2 local extension workers supported the coordinator. Delivery methods for the educational intervention included short videos, practical demonstrations, visual aids (pesticide labels, PPE, and spraying equipment), farmer experience sharing, breakout group exercises, and take-home infographic posters.

#### Step 4 of RANAS-Based Intervention Development: Procedures of RANAS-Based Text Messages

After the educational intervention was implemented, 20 SMS text messages were sent in increasing intervals from mid-February 2021 to September 2021 to the farmers assigned to 1 of the 2 arms that received the educational intervention. Figure 5 illustrates the procedure, targeted psychosocial determinants of behavior, and behavior change techniques. The first phase was implemented from February 2021 to March 2021 and aimed at motivating farmers to buy PPE (A1: action plan to buy PPE; A2: others’ behavior; call 1: action plan+monitoring of PPE purchase; B1: others’ behavior; B2: response efficacy, as indicated in the figure). The second phase was carried out from April 2021 to September 2021 with an emphasis on the use of PPE while handling pesticides during the spraying season (calls 2 and 3: monitoring of PPE use; B3: others’ behavior; B4: response efficacy; C1: others’ behavior; C2: overcoming barriers). The SMS text messages were automatically sent to the farmers’ phones according to the following timeline. In the first intensive week, we sent daily SMS text messages to refresh the RANAS framework and 2 KAP-related details that had been identified as relevant in the baseline assessments. These targeted beliefs about costs and benefits, descriptive and injunctive norm, attitudes toward pesticide toxicity (KAP), feelings (proud, not weak), knowledge of the best weather in which to use PPE (KAP), action knowledge, and action planning. Gradually decreasing the frequency of reminders, we then sent weekly; biweekly; and, finally, monthly SMS text messages. These alternatively targeted descriptive norm (others’ behavior), response efficacy, and barrier planning regarding PPE use. As one of the most relevant determinants was descriptive norm we wished to send real information about other farmers’ behavior to the participants, particularly other farmers’ extent of owning and using PPE. For this purpose, the participants were called 3 times during the SMS text messaging period to assess to what extent they owned and used PPE to later on share this information in SMS text messages with other farmers.

